## Abstract

**Background:**

Breast cancer is a prevalent form of cancer among women worldwide, often accompanied by physical and psychological side effects due to the disease and the treatment’s aggressiveness. Regular physical exercise has emerged as a non-pharmacological approach to improve the quality of life of breast cancer survivors. We herein report the protocol of the WaterMama Study, which aims to evaluate the effects of land- or water-based aerobic exercise programs, compared to a health education program, on cancer-related fatigue and other health-related outcomes in breast cancer survivors.

**Methods:**

The WaterMama trial is a randomized, single-blinded, three-arm, parallel, superiority trial. We aim to recruit 48 women ≥ 18 years of age who have completed primary treatment for stage I–III breast cancer. Participants are randomly allocated in a 1:1:1 ratio to 12-week interventions of aerobic exercise training programs either in the aquatic or land environment (two weekly 45-min sessions) plus health education (a weekly 45-min session), or an active-control group receiving health education alone (a weekly 45-min session). The primary outcome is cancer-related fatigue, and the secondary outcomes include cardiorespiratory fitness, muscular performance, muscle morphology, functional capacity, mental health, cognitive function, pain, and quality of life. Outcomes assessments are conducted before and after the 12-week intervention period. The analysis plan will employ an intention-to-treat approach and per protocol criteria.

**Discussion:**

Our conceptual hypothesis is that both aerobic exercise programs will positively impact primary and secondary outcomes compared to the health education group alone. Additionally, due to its multi-component nature, we expect the aquatic exercise program promote more significant effects than the land exercise program on cancer-related fatigue, muscular outcomes, and pain.

**Trial registration:**

The study was prospectively registered at ClinicalTrials.gov NCT05520515. Registered on August 26, 2022. https://clinicaltrials.gov/ct2/show/NCT05520515

## Administrative information

Note: the numbers in curly brackets in this protocol refer to SPIRIT checklist item numbers. The order of the items has been modified to group similar items (see http://www.equator-network.org/reporting-guidelines/spirit-2013-statement-defining-standard-protocol-items-for-clinical-trials/).

## Introduction

### Background and rationale {6a}

Breast cancer stands as the most prevalent cancer type among women worldwide. In 2022, it accounted for approximately 2.3 million new diagnoses, representing 23.8% of all new cases in women and the most frequent cause of death (666,103 deaths) across all age groups [1]. In Brazil, excluding non-melanoma skin tumors, it is the most incident cancer among women across all regions of the country. Projections for 2023 to 2025 estimate 73,610 new breast cancer cases in Brazil, corresponding to a risk of 66.54 new cases per 100,000 women [2].

Scientific evidence has confirmed that cancer treatment enhances survival rates [3]. However, survival is often accompanied by physical and psychological side effects caused by both the disease and the toxicity of the treatment. Persistent symptoms include exacerbated cancer-related fatigue, impaired quality of life, increased depressive and anxiety symptoms, and compromised ability to perform daily activities [4–10]. Notably, cancer-related fatigue is reported as one of the most substantial challenges faced by breast cancer survivors [11, 12], with a consequent negative impact on the health-related quality of life, underscoring the paramount importance of investigating this outcome within this population.

In this context, physical exercise is considered a non-pharmacological approach to improving health-related outcomes for cancer survivors [13]. Meta-analyses of several controlled intervention studies have demonstrated that physical exercise programs can improve cancer-related fatigue, physical fitness, and mental health in this population [11, 12, 14]. While evidence supporting the positive effects of exercise programs during and after breast cancer treatment has predominantly focused on land-based exercise programs (i.e., walking/running, cycling, resistance training) [15], there is growing interest in the potential benefits of water-based exercise programs for this population [16–19]. While original evidence is increasing in this area [20–29], there is a notable lack of studies comparing the effects of exercise programs in aquatic and land environments for breast cancer survivors [24, 26].

An important characteristic of the aquatic environment is the lower apparent weight resulting from water immersion, corresponding to around 20 to 30% of the total body weight on land in women with different age ranges and body compositions [30, 31]. This substantially reduced load to be supported during water-based exercises facilitates exercise performance and reduces osteoarticular impact. Additionally, the physical properties of the aquatic environment provide analgesic effects in a pleasant setting [20], promoting well-being and favoring adherence to exercise programs. The large sensory flow in water may be responsible for reduced pain perception, with pain modulation affected by factors such as water temperature and turbulence (therapeutic effect of hydromassage) [32]. This aspect may be particularly beneficial for breast cancer survivors undergoing hormonal therapy, as joint pain and other musculoskeletal disorders may arise as possible adverse effects [33].

Moreover, water-based exercises may offer advantages due to their multi-component nature. A program involving aerobic exercises performed in water can yield improvements not only in cardiorespiratory parameters but also in flexibility, balance, and muscle strength, thickness, and quality [34–36]. These characteristics may be attributed to the water’s physical properties, such as drag force and buoyancy, which provide a multidirectional resistance and a higher instability than the land environment during exercise performance [37]. Although such outcomes were primarily investigated in older populations, it is plausible that these findings may be applicable to breast cancer survivors. Considering the physical and psychological impairments in breast cancer survivors, it is pertinent to investigate if exercise programs performed in the aquatic environment may potentiate health-related benefits.

### Objectives {7}

We aim to analyze the effects of 12 weeks of land- or water-based exercise programs compared with a health education program alone on cancer-related fatigue, cardiorespiratory fitness, muscular performance, muscle morphology, functional performance, mental health, cognitive function, pain, and quality of life in breast cancer survivors. Herein, we report the protocol of the WaterMama Study, a superiority randomized clinical trial with three parallel groups, using cancer-related fatigue as the primary outcome. Based on the intervention design and outcomes of interest, we hypothesize that both training programs will significantly improve the investigated outcomes compared to the health education group alone. Additionally, we expect the water-based exercise program to have a more significant positive impact on cancer-related fatigue and physical parameters due to its multi-component nature.

### Trial design {8}

The WaterMama trial is a randomized clinical trial employing a 1:1:1 allocation ratio. It was designed as a superiority trial with three parallel groups, controlled by active intervention, and blinded to outcome assessors and data analysts.

## Methods: participants, interventions, and outcomes

### Study setting {9}

This trial is being conducted at the Escola Superior de Educação Física e Fisioterapia (ESEF) of the Universidade Federal de Pelotas (UFPel), Brazil.

### Eligibility criteria {10}

The inclusion and exclusion criteria for participants are outlined as follows.

#### Inclusion criteria

Women diagnosed with stage I–III breast cancerAged 18 years or olderHave completed primary treatment for breast cancer (including surgery, chemotherapy, and/or radiotherapy) within the past 24 months before the start of the intervention, regardless of hormonal treatment statusWillingness to participate in either intervention group and absence of fear of the aquatic environment

#### Exclusion criteria

Active metastatic or locoregional diseasePresence of major psychiatric or cognitive disordersSevere nausea, anorexia, or any other condition that impedes participation in the exerciseRegular engagement in exercise within the last 3 months

### Who will take informed consent? {26a}

During the recruitment process, potential participants are invited to visit the Laboratório de Avaliação Neuromuscular (LabNeuro) at ESEF/UFPel after the initial phone contact and screening to verify eligibility criteria. During this visit, one of the responsible researchers ([name] or [name]) provides detailed information about the research procedures, including potential risks and benefits, and addresses any possible questions. Finally, participants are asked to sign an informed consent form if they agree to participate.

### Additional consent provisions for collection and use of participant data and biological specimens {26b}

Not applicable. All necessary consent for data collection is included in the primary informed consent, and no biological specimens will be collected.

## Interventions

### Explanation for the choice of comparators {6b}

Participants are allocated after randomization into one of three groups: a water-based exercise training group, a land-based exercise training group, or a health education active control group, all lasting for 12 weeks. The choice of a land-based training group is a crucial comparator in this study. Comparing the outcomes of an aquatic program with those of a land program allows a comprehensive assessment of the potential additional benefits conferred by the aquatic environment. A land-based comparator will allow discerning whether the unique physical properties of water, such as drag force and buoyancy, offer advantages beyond those achievable through traditional land-based exercises. In addition, the decision to incorporate a health education comparator was motivated by the need to have a control group that does not engage in exercise but still receives some form of intervention. By selecting health education as the active comparator, we acknowledge the importance of not only physical exercise but also health education and awareness in promoting overall well-being. To ensure that the effect of the health education intervention did not make this group substantially different from the others, activities from the health education group were similarly integrated into the other intervention groups.

### Intervention description {11a}

#### Active control group: health education program

The health education sessions take place at the ESEF/UFPel. Participants from the active control group engage in an educational program consisting of 45-min lectures once a week. These lectures are led by a qualified health professional following a structured content script using both expository and interactive approaches. The topics covered include breast cancer symptoms and therapeutic management. Participants also receive a customized booklet (available in press and digital formats) at the study’s onset containing the lecture topics presented in Table 1.

**Table 1 Tab1:** Topics covered in the health education intervention

Topics in health education for hypertension
1. Body image
2. Arm, breast, and vasomotor symptoms
3. Quality of life
4. Eating habits
5. Cancer-related fatigue
6. Integrative and complementary practices
7. Cognitive function
8. Quality of sleep
9. Depressive and anxiety symptoms
10. Pain and arthralgia
11. Sexuality
12. Physical activity and exercise

#### Exercise intervention groups: water- and land-based exercise programs

Participants of both exercise intervention groups undertake a 12-week exercise program with two weekly sessions on non-consecutive days, regardless of the exercise environment. Each session lasts 45 min and comprises a 5-min warm-up, 35 min of aerobic exercises, and a 5-min stretching routine throughout the intervention. In addition, both exercise intervention groups participate in the same educational program as the health education group, receiving lectures separately without interacting with the other groups.

Training intensity is prescribed using Borg’s 6–20 rating of perceived exertion (RPE) scale. This method was chosen due to the physiological changes induced by immersion, such as heart rate (HR) alterations, requiring specific maximal tests in each environment to determine the HR training target [38]. RPE provides a valid tool for intensity control, exhibiting similar indexes at submaximal and maximal intensities between environments [39]. Studies employing RPE to prescribe water-based aerobic training have revealed positive effects on cardiorespiratory, neuromuscular, and functional parameters in various populations [35, 36].

The exercise program’s periodization was adapted from those proposed by Andrade et al. [35], as detailed in Table 2. This strategy periodization is based on interval training, alternating between high-intensity effort stimulus and low-intensity active recovery phases. To ensure controlled progression of external load throughout the exercise interventions in aquatic and land environments, the number of repetitions and the distance covered during the first minute of the intensity stimulus in the first and seventh sets were individually recorded at the last session of each mesocycle (sessions 6, 12, 18, and 24).

**Table 2 Tab2:** 12-week aerobic exercises duration

Weeks	Sets	Intensity	Duration
1–3	7	4 min RPE 13 + 1 min RPE 11	35 min
4–6	7	4 min RPE 14 + 1 min RPE 11	35 min
7–9	7	4 min RPE 15 + 1 min RPE 11	35 min
10–12	7	4 min RPE 16 + 1 min RPE 11	35 min

*RPE* rating of perceived exertion

##### Water-based exercise program

The intervention takes place at the thermal pool of the Brilhante Club in Pelotas City. The pool water temperature is maintained between 30 and 32 °C, with participants immersed to a depth level between the xiphoid process and shoulders. The water-based exercise session comprises the following exercises sequence: stationary running, frontal kick, cross-country skiing, and butt kick during the stimulus, and jumping jacks during the active recovery. These exercises are commonly used, featuring stationary execution, and offer safe osteoarticular impact loads suitable for women of different age and body composition ranges [30, 31]. The exercise sessions are conducted in small groups, with a maximum of eight participants, supervised by two experienced instructors, one outside and one inside the pool. An RPE scale (banner 0.60 × 0.90 m) is fixed outside the pool in front of the participants.

##### Land-based exercise program

The intervention takes place at the multi-sport gym of the ESEF/UFPel. The land-based exercise session comprises walking/running on the court. The exercise sessions are conducted in small groups, with a maximum of eight participants, supervised by two experienced instructors, one positioned in each corner of the court. An RPE scale (banner 0.60 × 0.90 m) is fixed at the corner corresponding to the starting point.

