### Sample size {14}

The sample calculation was conducted using the GPower version 3.1 program, adopting a significance level of *α* = 0.05 and 90% power. Data for the calculation were derived from the study results by Kessels et al. [12] for the primary outcome of cancer-related fatigue (effect size 0.605). It resulted in a total sample size of 39 subjects. Additionally, nine individuals (approximately 20%) will be included in the study to account for potential sample losses, totaling 48 participants randomized into the three groups.

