## Statistical methods

### Statistical methods for primary and secondary outcomes {20a}

We will use descriptive statistics, including mean, standard deviation, 95% confidence intervals, and absolute or relative frequencies as applicable. The Shapiro–Wilk and Levene tests will be used to assess data normality and homogeneity. Generalized estimating equations, with Bonferroni adjustment for post hoc tests, will be used to compare time points and groups. One-way ANOVA and/or Kruskal–Wallis tests will be conducted to compare training compliance and follow-up questionnaire responses between groups. Effect sizes between groups will be calculated based on the absolute difference (± SD) between baseline and post-intervention values, using Cohen’s *d*. All statistics procedures will be performed in the SPSS vs. 28.0, with a significance level set at *α* = 0.05.

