### Frequency and plans for auditing trial conduct {23}

Due to limited resources, the WaterMama Study does not have planned conducting auditing trial. However, the Project Management Group meets at least twice per semester (before and after each wave of intervention) to review the trial conduct.

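### Exercise is delivered in arm-specific classes of up to eight, but the sample size assumes independent women and the described GEE has no class term; add a class-effect sensitivity analysis and state the power assumption

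*Protocol article*

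**What the plan says.** All references are to the Protocol article. Allocation is individual, 1:1:1 (Trial design {8}; Sequence generation {16a}). After allocation, exercise is a group activity. The Land-based exercise program section says "The exercise sessions are conducted in small groups, with a maximum of eight participants", and the Water-based exercise program section describes "small groups, with a maximum of eight participants, supervised by two experienced instructors". The description of the exercise arms adds that their lectures are given apart from the other groups. Frequency and plans for auditing trial conduct {23} refers to meetings "before and after each wave of intervention", so delivery is staggered. A class is therefore nested within one arm.

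Sample size {14} works from "adopting a significance level of *α* = 0.05 and 90% power" and an effect size of 0.605. "It resulted in a total sample size of 39 subjects", and "nine individuals (approximately 20%) will be included in the study to account for potential sample losses", giving 48. It mentions neither an ICC nor a design effect.

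Statistical methods {20a} says "Generalized estimating equations, with Bonferroni adjustment for post hoc tests, will be used to compare time points and groups". It names no class term and does not say which unit the GEE clusters on. Methods for additional analyses {20b} plans none.

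**The concern.** Women in one class share two instructors, a set of peers and a time of year over 24 sessions. The protocol itself takes peers to be possibly influential: its follow-up questionnaire asks about intervention partners. The primary outcome, the Piper Fatigue Scale (PFS), is self-reported by participants who know their arm, so some similarity between classmates is plausible.

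Because each class belongs to a single arm, any class effect goes straight into the arm mean. Variation between classes is then part of the error of every contrast involving an exercise arm. It matters most for water versus land, an explicit hypothesis for fatigue, where both sides are delivered in classes.

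Two separate consequences are at stake. An analysis that ignores class is anti-conservative. An analysis that allows for class is valid but has less power than the plan states.

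**Working it through.** **Inputs from the protocol.** Three arms; α = 0.05; power 90%; effect size 0.605; calculated N = 39 (13 per arm); 48 randomised (16 per arm); exercise classes of at most 8.

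**Assumed, because the protocol gives no figure.** ICC of 0.01, 0.05 or 0.10; class size m of 4 or 8.

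**Step 1: reproduce the plan's figure.** One-way ANOVA, k = 3, Cohen's f = 0.605, noncentral F with λ = f²N:

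- λ = 0.605² × 39 = 0.366 × 39 = 14.27
- critical F(2, 36) = 3.26
- power = 0.910

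The smallest balanced N that reaches 90% is 39. A within–between repeated-measures calculation (f = 0.3025, two time points, correlation 0.5) gives the same N and power. Both treat women as independent, so the stated figure contains no allowance for class.

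**Step 2: allow for class.** Design effect DE = 1 + (m − 1) × ICC. The true standard error is √DE times the one that ignores class, and λ becomes 14.27/DE. Power uses 2 and 36 df and applies DE in all three arms.

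**Step 3: type I error if class is ignored.** Null trials were simulated (60,000 per setting) with 16 women per arm and equal class sizes in all three arms. The three pairwise t-tests were each run at 0.05/3, to mirror the planned Bonferroni step; they stand in for the GEE. With no clustering the familywise error is about 4.3%.

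| m | ICC | DE | √DE | λ | Class-adjusted power, N = 39 | Familywise error, class ignored |
|---|---|---|---|---|---|---|
| 4 | 0.01 | 1.03 | 1.015 | 13.86 | 0.90 | about 5% |
| 4 | 0.05 | 1.15 | 1.072 | 12.41 | 0.87 | about 6.5% |
| 4 | 0.10 | 1.30 | 1.140 | 10.98 | 0.82 | about 9% |
| 8 | 0.01 | 1.07 | 1.034 | 13.34 | 0.89 | about 5% |
| 8 | 0.05 | 1.35 | 1.162 | 10.57 | 0.80 | about 10% |
| 8 | 0.10 | 1.70 | 1.304 | 8.40 | 0.70 | about 16% |

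**Step 4: degrees of freedom.** The power column is optimistic, because it keeps individual-level df. With two classes per arm (average size 6.5) there are six classes and 6 − 3 = 3 class-level df. Power at N = 39 is then about 0.42 at ICC 0.05, and only about 0.50 even at ICC 0. Most of that loss comes from having few classes, not from the correlation itself.

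**The case against.** The other side has a good deal right.

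- **The GEE.** The article condenses the analysis into one sentence. It does not name the clustering unit, and model detail may sit in a fuller document. A reader might infer that the GEE certainly treats women as independent. That is the natural reading of a model comparing time points and groups, but it is not stated. The independence assumption in the sample size is firmer, because the number reproduces.
- **The ICC.** A reader might infer that the standard errors are too small and that type I error exceeds 5%. Neither follows without a positive ICC. At 0.01 the power is 0.89–0.90, in effect the planned figure.
- **Class size.** Eight is a ceiling. The project group meets at least twice per semester, around each wave, which suggests about one wave per semester. Recruitment runs from January 2023 to August 2024. Sixteen women over three or four waves is 16/3 ≈ 5 or 16/4 = 4 per class, so the rows for four may be nearer the truth.
- **Bonferroni.** At 0.05/3 and ICC 0.05, the error per contrast is 3.9% (two classes of eight) or 2.6% (four of four). Both lie below 5%, though above the 1.67% that each test is meant to have. At ICC 0.10 they are 6.8% and 3.6%.
- **The control arm.** No lecture group size is given. If control women are independent, the unadjusted error of an exercise-versus-control test at ICC 0.05 is about 7.1% (classes of eight) or 5.8% (classes of four), lower than with clustering in both arms.
- **Losses.** If all 48 women are analysed, class-adjusted power with classes of eight is 0.95, 0.89 and 0.80 at ICC 0.01, 0.05 and 0.10.

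What remains is that arm-specific classes exist, the power calculation ignores them, and nothing in the described analysis would reveal their effect.

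**Conclusion.** The point holds conditionally. With a positive within-class ICC, ignoring class understates between-arm standard errors: the true ones are 1.5–14% larger with classes of four and 3–30% larger with classes of eight over ICC 0.01–0.10. The 90% also overstates the power of a valid class-adjusted test. The effect is negligible at ICC 0.01 and becomes material by about 0.05, especially if classes are near the ceiling.

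Two further inferences should be resisted. First, inflated type I error and lost power do not occur together in one analysis. In simulation with classes of seven and six per arm, the rejection rate of the unadjusted F test under the planned effect stayed at 0.89–0.91 for ICCs up to 0.10; power falls only once class is modelled. Second, the absence of a wave term is not the fault. A wave effect shared by all arms does not inflate between-arm error; the arm-specific class does.

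These sizes rest on assumed ICCs and class sizes, on 0.605 entering the calculation as Cohen's f, and on clustering in all three arms. This is a cheap improvement to the plan, not evidence that the primary analysis is invalid.

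**What to change.** 1. Keep the planned GEE as the primary analysis.
2. Record each woman's class, and her lecture group in the control arm if lectures are given to fixed groups.
3. Prespecify one sensitivity analysis of the PFS contrasts: a linear mixed model with a random effect for class in the exercise arms (and for lecture group in the control arm where that applies), with Kenward–Roger or Satterthwaite df. Report the estimated ICC.
4. In Sample size {14}, state that the 90% power assumes no within-class correlation, and give the power over a range of ICCs and class sizes, as in the table above.

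A fixed factor for wave is not needed for this purpose. The cost is one identifier that the team should already hold, one extra model and a sentence or two of text, with no additional participants. The drawback is that, with few classes per arm, the sensitivity interval will be wide and the ICC poorly estimated, which is why this should be a sensitivity analysis and not replace the primary one.
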